#### Statistical Methods for Primary and Secondary Outcomes

The aim of this study is to compare clinical outcomes between classes from a middle school sensitized to HPV vaccination through a combined health promotion program (intervention group) and a middle school without any specific action (control group). The null hypothesis is that there is no difference in the groups. For descriptive analyses, qualitative variables will be described in terms of frequencies and percentages with their 95% confidence intervals; quantitative variables will be expressed in terms of means, standard deviations, and 95% confidence intervals or in terms of medians and IQRs (25th and 75th percentiles).

Comparability of groups at inclusion will be checked: bivariate comparisons of categorical variables will be performed by the chi-square test or Fisher exact test, depending on the conditions of application. Bivariate comparisons of means will be performed by the Student *t* test or Mann-Whitney *U* test, depending on the conditions of application. For the analysis of the primary outcome: the proportion of schoolgirls who will have completed the full HPV vaccination regimen at the end of the school year will be compared between the 2 groups (intervention and control) by the chi-square test or Fisher exact test, according to validity conditions.

Concerning secondary outcomes analysis: the proportion of schoolgirls who initiated HPV vaccination (1 dose) by the end of school year will be compared between the 2 groups (intervention and control) by the chi-square test or Fisher exact test according to validity conditions. The proportion of boys who will have completed the full vaccination schedule at the end of school year will be compared between the 2 groups (intervention and control) by the chi-square test or Fisher exact test, according to validity conditions. The proportion of boys who will have initiated the vaccination scheme at the end of the school year will be compared between the 2 groups (intervention and control) by the chi-square test or Fisher exact test, depending on the conditions of validity.

The analysis of barriers to vaccination will describe the causes of nonvaccination reported for students who did not initiate the vaccination schedule. Analyses will be performed for girls and boys separately. We will also compare sociodemographic data, medical history, and health care utilization data between students who initiated HPV vaccination at the end of the school year and those who did not in the intervention group. Bivariate comparisons of percentages will be performed by the chi-square test or Fisher exact test depending on validity conditions. For continuous variables, comparisons will be made using the Student *t* test or the Mann-Whitney *U* test, depending on the conditions of validity. A multivariate analysis by logistic regression will be carried out in order to take into account confounding phenomena: the variable to be explained will be the fact of having initiated vaccination at the end of the school year, and the explanatory variables entered in the model will be the variables for which the significance threshold in bivariate analysis will be ≤.20.

To be determined in the intervention group: among students who initiated HPV vaccination at the end of school year, the proportion of students who used the health bus to initiate this vaccination. Among students who completed the full vaccination schedule at the end of school year, we will determine the proportion who completed all injections on the health bus.

In the intervention group, the proportion of students who used the health bus for sexual health information will be evaluated. In the intervention group, positive and negative points reported by students, their parents, and school staff about this program will be described. Proportion of students up to date for each type of vaccine (according to current vaccination calendar) at the end of school year, in the entire study population as well as in each of the 2 groups (intervention and control), and comparison of these proportions between the 2 groups by the chi-square test or Fisher exact test will be determined, according to validity conditions.

Analyses comparing control group to intervention group will all be performed on an intention-to-treat basis. All hypotheses will be tested with bilateral tests and *α*=.05 and confidence interval calculated at 95%. Analyses will be performed using SAS (version 9.4, SAS Institute Inc) software.

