## Methods

### Trial Design

This study is a cluster controlled intervention study using a superiority design. Children who will attend the combined health promotion program will constitute the intervention group and will be compared with children who will not attend the program (as is currently the case in all French middle schools), who will constitute the control group.

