### Study Setting

This trial will concern Reunion Island in order to investigate the particular epidemiological situation of HPV on the island, even if the results of this study are expected to be applicable to other French regions.

The 2 arms of the trial will be designed to have the most comparable populations and to avoid any risk of contamination between the 2 arms or having general practitioners taking care of children in both schools.

We have thus chosen to carry out a cluster trial. The 2 groups (intervention group and control group) will be selected from a middle schools located in each of 2 cities. In each of the schools, we will randomly draw 3 classes in each grade level (6th, 7th, 8th, and 9th grade) to have a balanced number of students in each arm (see sample size). Thus, 12 classes will be selected for each school.

Provided that there is a relationship between socioeconomic status and vaccination coverage, it was decided to focus the study only on middle schools in priority education zones, which theoretically enroll a population in which HPV vaccination coverage is the lowest. On Reunion Island, 21 middle schools are classified as priority education zones, spread over 7 cities. In agreement with the head of the academy and the school directors, 2 schools have been designated among the abovementioned middle schools: the intervention school will be Paul Hermann Middle School, located in St Pierre, and the control school will be Plateau Goyave Middle School, located in St Louis.

These choices are based on the schools’ ability to participate in this research, their geographical location, and the ability to park the health bus at or in the immediate surroundings of the school of the intervention group. The health bus will be provided by the Association d’Education Thérapeutique et d’Intervention Sociale (ASETIS, or Association for Therapeutic Education and Social Intervention), existing since 1996 and recognized as being of public interest.

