### Statistical Analyses

#### Sample Size

To our knowledge, there are no recent studies that have evaluated the impact of school-based vaccination on HPV vaccination coverage rates. An experimental catch-up vaccination program (diphtheria, tetanus, poliomyelitis, pertussis, measles, mumps, rubella, meningococcus C, hepatitis B, and HPV) in schools in the Vosges (Eastern France) [18] showed a participation rate ranging from 42.9% in the first year to 29% in the second year.

The calculation of the study size is based on the expected proportion of vaccination among girls, as this is the main objective of this study and we have no data for vaccination among boys at this time. Statistical assumptions were as follow:

Proportion of schoolgirls who have had a complete HPV vaccination schedule at the end of school year of 6% in the control group for all students (compared to the 8.1% expected at age 16 years [12])Proportion of schoolgirls with a complete HPV vaccination schedule at the end of the school year of 20% in the intervention group

Thus, 87 girls in each group would need to be included to demonstrate this 14% difference at *α*=.05 and power (1−β=0.80). Assuming 15% nonanalyzable data (lost to follow-up, nonresponse), a total of 103 female students per group would need to be included. As there are roughly as many girls as boys in each class, we would need to include 206 students per group. In order to have an equal representation of each age group, the sampling will be stratified in the grades: 6th, 7th, 8th, and 9th grade. Thus, 52 students per grade and per group should be included.

If we consider that the classes contain an average of 22 students each, a minimum of 3 classes per grade should be randomly selected in each of the 2 middle schools to ensure the minimum necessary recruitment. Thus, randomly selecting 3 classes per grade in each of the 2 middle schools will make it possible to include approximately 132 female students per group and thus to ensure the minimum necessary recruitment. A total of 528 students are expected to be recruited (264 girls [132 per group] and 264 boys [132 per group]). The calculation of the number of subjects required was performed with PASS (version 15, NCSS) software.

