#### Sequence Generation

In priority education schools, there are classes called Sections d’enseignement general et professionnel adapté (SEGPA; adapted general and vocational education sections): these classes, from 6th to 9th grade, are integrated into the middle school. They welcome young people who have significant school difficulties that cannot be resolved by academic assistance and support. There is only a small group of students (16 maximum) in each class in order to individualize each student's progress. SEGPA classes should enable students to access at least a professional qualification.

In the Paul Hermann Middle School, there are 9 classes in each grade, including 2 classes of SEGPA per grade. In the Plateau Goyave Middle School, there are 9 classes in 6th grade and 9th grade and 10 classes in 7th and 8th grade, including 2-3 classes of SEGPA per grade. In each of the selected middle schools, 12 classes will be randomly selected in order to have a balanced number of students in each arm.

In order to have an equal representation of each age group, the sampling will be stratified on the grade (6th, 7th, 8th, and 9th grade), and in order to take into account the specificities of SEGPA classes, we decided to stratify on SEGPA classes as well. As the main point in this comparative trial was similarity of the 2 groups compared, we decided to randomly select 1 SEGPA class per grade and 2 non-SEGPA classes per grade. Thus we will include in this trial 256 students from Paul Hermann Middle School (intervention group) and 255 students from Plateau Goyave Middle School (control group).

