### Strengths and Limitations

This protocol is submitted more than a year after recruitment began, since sanitary COVID-19 condition was in constant change and evolution and it was difficult to know whether we could continue the process of the trial. Amendments were made and submitted to the ethics committee, facing prohibition of meetings with more than 6 people. This protocol is the result of our constant adaptation to these different obstacles.

Having different exclusion criteria for participants in the intervention and control arms m ay introduce a selection bias by design. However, we wanted to include as many children as possible in the control group to have a representative sample of the population, and the groups may still be comparable. The sample size calculation has not taken into account correlation between participants in the same cluster. As such, the sample size is likely to be too small. However, one limit is the price of the vaccine, which limited our ability to include more students, with regard to the funds allocated.

On Reunion Island, specificities regarding economic and societal development are as follows: high rate of universal health insurance coverage where the high cost of HPV vaccine may be a barrier, mixed culture with religious faith incompatible with premarital sex and racist biopolitical mistrust of the West from which the vaccine comes from, and the particular weight of the antivaccine leagues which casted a negative halo around the subject [25]. Thus we expect a strong veto from parents.

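### The primary analysis tests individual girls with a chi-square or Fisher test although whole classes were drawn from one school per arm, so its p-value and confidence interval overstate the certainty

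*Protocol article*

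**What the plan says.** Under Trial Design the article states: "This study is a cluster controlled intervention study using a superiority design". Study Setting explains that the arms were separated to avoid contamination and adds "We have thus chosen to carry out a cluster trial". The schools were not randomised: "2 schools have been designated among the abovementioned middle schools", one for each arm. Classes were then sampled inside each school ("Thus, 12 classes will be selected for each school"), and Sequence Generation gives the quota: "we decided to randomly select 1 SEGPA class per grade and 2 non-SEGPA classes per grade".

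Under Statistical Methods for Primary and Secondary Outcomes, the proportion of girls with a complete schedule "will be compared between the 2 groups (intervention and control) by the chi-square test or Fisher exact test, according to validity conditions". Initiation among girls, completion and initiation among boys, and coverage for other vaccines are compared in the same way, two-sided at 5% with 95% confidence intervals. The only model in the plan is a logistic regression for initiation within the intervention group. It does not serve the primary comparison and has no term for class.

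Strengths and Limitations concedes one part of the problem: "The sample size calculation has not taken into account correlation between participants in the same cluster". It concludes that the sample may be too small and says nothing about the analysis.

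**The concern.** The program is delivered to a whole school and the sample consists of whole classes. Girls in one class share teachers, the information session, the bus timetable and each other's opinions, so their vaccination outcomes are likely to be correlated. The named tests contain no term for class, school or sampling stratum. The limitation that the authors disclose concerns power, that is, the risk of missing an effect. Ignoring the same correlation in the analysis creates the opposite risk of declaring an effect too readily, and the article does not mention it.

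There is a second layer. With one school per arm, any difference between the two schools is fully confounded with the program. A significant result could reflect class variation, school variation or the program. The abstract's Conclusions and Future Directions name extension to all middle schools on the island as the final implication, so an overstated p-value would feed a policy decision.

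**Working it through.** **1. The plan's own figure.** Sample Size gives 6% (control) versus 20% (intervention), two-sided α = 0.05 and power 0.80. The individual-level formula with unpooled variance is

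n = (1.960 + 0.842)² × [0.06×0.94 + 0.20×0.80] / 0.14² = 7.849 × 0.2164 / 0.0196 = 86.7, rounded up to 87.

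With 15% non-analysable data, 87 / 0.85 = 102.4, rounded up to 103. Both stated figures reproduce with no design effect, so neither the sample size nor the test allows for clustering.

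**2. Class level, by formula.** The article says "the classes contain an average of 22 students each", so about 11 girls per class, and 12 × 11 = 132 girls per arm. With m = 11, the design effect is DE = 1 + (m − 1) × ICC. The true error of the nominal 5% test is 2 × [1 − Φ(1.96/√DE)], and a correct interval is √DE times as wide. The ICC values are assumed.

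| Class ICC | DE | True error | Interval factor | Effective girls per arm |
|---|---|---|---|---|
| 0.01 | 1.10 | 6.2% | 1.05 | 120 |
| 0.02 | 1.20 | 7.4% | 1.10 | 110 |
| 0.05 | 1.50 | 11.0% | 1.22 | 88 |
| 0.10 | 2.00 | 16.6% | 1.41 | 66 |

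**3. Class level, by simulation.** Allowing for 15% loss, 11 × 0.85 = 9.35, so 9 analysable girls per class. Beta-binomial simulation (40,000 runs, 12 classes of 9 girls per arm, no program effect, coverage 6% and 13%) gave these rejection rates:

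| Class ICC | Chi-square test |
|---|---|
| 0.02 | about 6–7% |
| 0.05 | about 9–10% |
| 0.10 | about 14–15% |
| 0.20 | about 22–23% |

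Switching to Fisher when an expected count falls below 5 lowers these by at most about 2 points. A t test on the 24 class proportions stayed at about 3.5–5.0% throughout.

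**4. School level.** Take 104 girls per arm and coverage p = 0.06. The sampling variance of one arm's proportion is 0.06×0.94/104 = 0.000542. A between-school standard deviation s adds s², so r = √[(0.000542 + s²)/0.000542] and the true error is 2 × [1 − Φ(1.96/r)].

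- s = 0.02: r = √(0.000942/0.000542) = 1.318, and 1.96/1.318 = 1.487, giving 13.7%.
- s = 0.03: r = √(0.001442/0.000542) = 1.631, and 1.96/1.631 = 1.202, giving 22.9%.

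Expressed as an ICC with 132 girls per arm, a school-level value of only 0.01 gives DE = 1 + 131 × 0.01 = 2.31 and an error of about 20%. With one school per arm, the between-school variance has zero degrees of freedom.

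**5. The interval at the planned effect.** With 132 girls per arm, the naive half-width is 1.96 × √(0.2164/132) = 7.9 points. At class ICC 0.05 it is 7.9 × 1.22 = 9.7 points; at 0.10 it is 7.9 × 1.41 = 11.2 points. Adding 2s² to the naive variance for the two schools gives 1.96 × √(0.001639 + 2×0.03²) = 11.5 points at s = 0.03.

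**The case against.** The strongest reply is about size. Both schools use the same quota of one SEGPA and two non-SEGPA classes in each grade, so variation due to grade and SEGPA is largely balanced between arms and does not inflate the difference. If half the class variance lay between those strata (an assumption), the simulated chi-square error at 6% coverage would fall to 5.7%, 6.7%, 8.9% and 12.8% at ICCs of 0.02, 0.05, 0.10 and 0.20. The article gives no ICC, and at 0.01 the inflation is mild. If inference is confined to these two schools, sampling about a third of the classes also shrinks the class component. These points stand: the simulated rates for exchangeable classes lie towards the upper end. They reduce the inflation without removing it.

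Second, the confounding of school with program comes from the design, and no class-level analysis repairs it. That is correct, so it belongs in a stated limitation with a sensitivity range. It is not something the new test can cure.

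Third, the island-wide extension is worded as an aspiration and not as a planned inference. That is fair, but the trial result is still what would support it.

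Fourth, about 0.06 × 104 = 6 events are expected in the control arm across 12 classes. Mixed models or generalised estimating equations with several covariates would be fragile. This stands and guides the choice of analysis below.

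An unseen analysis plan is no answer, because the article names the primary test outright.

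**Conclusion.** The concern holds. The plan fixes a test that assumes independence for a sample it describes as clustered, and the disclosed limitation covers the sample size only. For any positive net correlation within arms, the p-value is too small and the interval too narrow.

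The class-level part ranges from mild (about 6–7% error at ICC 0.02) to serious (14–15% at 0.10, 22–23% at 0.20). This assumes 9 analysable girls per class and no offset from the balanced quotas, with ICC values that are assumed throughout. The school-level part may be larger, at about 14% or 23% for a between-school standard deviation of 2 or 3 points, and these data cannot estimate it.

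This does not mean that the trial must fail. At class ICC 0.05, power with 132 girls per arm is still about 79%. A true 14-point difference could survive either widening shown above, since the half-widths remain below 14 points. The correction is nevertheless needed before the primary result is reported, because it affects the primary p-value and interval and every other between-group comparison.

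**What to change.** Make one cluster-level analysis primary: a linear model on the 24 class completion proportions with arm, grade and SEGPA status as terms. This leaves 24 − 6 = 18 residual degrees of freedom (intercept, arm, three for grade, one for SEGPA). Report the risk difference with its 95% interval from the t distribution. Working with class proportions avoids fitting a sparse-event model. Use the same approach for the other between-group comparisons and keep the chi-square or Fisher results as descriptive only.

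State that between-school variance cannot be estimated. Show how the interval widens for assumed between-school standard deviations of 1 to 4 percentage points, by adding 2s² to the variance of the difference. Limit the conclusion to these two schools and present island-wide extension as a question for a study with several schools per arm.

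The cost is revised analysis wording and a few lines of SAS code on data already held. The downsides are wider intervals, a more modest conclusion and equal weight for each class whatever its size. Because Results reports that recruitment is complete and analyses are under way, the change should be dated and labelled as made after data collection, with the originally planned test shown alongside.

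### The model of vaccination initiation picks its confounders by a bivariate p ≤ .20 screen and, as described, makes no allowance for the sampling of whole classes

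*Protocol article*

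**What the plan says.** The rule is in the protocol article, Statistical Methods for Primary and Secondary Outcomes, in the paragraph on barriers to vaccination.

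- That paragraph first describes the reported causes of nonvaccination and adds "Analyses will be performed for girls and boys separately".
- It then sets out a further comparison, restricted to the intervention group: "We will also compare sociodemographic data, medical history, and health care utilization data between students who initiated HPV vaccination" and those who did not.
- A logistic regression follows, with confounding given as its reason. For its outcome, "the variable to be explained will be the fact of having initiated vaccination at the end of the school year". For its covariates, "the explanatory variables entered in the model will be the variables for which the significance threshold in bivariate analysis will be ≤.20".
- On testing in general, "All hypotheses will be tested with bilateral tests", at α = .05.

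The article gives no number of candidate variables, no initiation rate and no allowance for class in this model. Sequence Generation says that 12 classes per school are drawn, stratified by grade and by SEGPA (adapted general and vocational education) status.

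**The concern.** A confounder is defined by its relation to both the exposure of interest and the outcome, and a crude p-value against the outcome does not measure that. A variable whose crude association is cancelled by another variable fails the screen, although adjustment needs it. A variable with no association passes one time in five. The final model is then read as if its covariates had been fixed in advance, so the intervals and p-values of the survivors are optimistic.

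Two features of the design add to this. The number of events may be small relative to the number of candidates, which makes odds ratios unstable. Students are also sampled as whole classes, so covariates that are constant within a class, such as grade or SEGPA status, carry less information than the student count suggests.

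At stake is how far the reported predictors of initiation can be trusted. Describing barriers is a listed secondary objective, and Future Directions says that the analysis of barriers will be used to improve the program.

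**Working it through.** **1. The plan's own sample size.** The inputs from Sample Size are 6% in controls ("complete HPV vaccination schedule at the end of school year of 6% in the control group for all students") and 20% in the intervention group ("Proportion of schoolgirls with a complete HPV vaccination schedule at the end of the school year of 20% in the intervention group"), with two-sided α = .05 and power 0.80. The unpooled formula gives n = (1.960 + 0.842)² × (0.06 × 0.94 + 0.20 × 0.80) / 0.14² = 7.849 × 0.2164 / 0.0196 = 86.7, so 87 per group. With 15% nonanalyzable, 87 / 0.85 = 102.4, so 103. Both figures reproduce. They concern completion in girls, whereas the model's event is initiation.

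**2. Events available to the model.** Initiation cannot be lower than completion, so 20% serves as a low reference for girls. The second reference is the participation of the earlier school catch-up program cited in Sample Size, 29% to 42.9%. Applying it to initiation here is an assumption.

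| Girls in the intervention group | at 20% | at 29% | at 42.9% |
|---|---|---|---|
| 132 (expected recruitment) | 26.4 | 38.3 | 56.6 |
| 122.5 (half of the 245 selected) | 24.5 | 35.5 | 52.6 |
| 103 (required, inflated) | 20.6 | 29.9 | 44.2 |
| 87 (required, analysable) | 17.4 | 25.2 | 37.3 |

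No figure can be given for boys, because the article states that it has no data on them. If there were 10 to 20 candidates (an assumption), 26.4 events would mean 2.6 to 1.3 events per candidate.

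**3. What the screen does to null covariates.** Because p < .05 implies p ≤ .20, a null variable that has passed the screen reaches p < .05 with probability of about 0.05 / 0.20 = 25%. A simulation supports this. It used independent null covariates, half binary and half continuous, a bivariate screen at .20, then logistic regression read at .05, with 500 data sets per setting.

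| Setting | Candidates | Mean number entering | p < .05 among those entering | p < .05 per candidate | At least one p < .05 |
|---|---|---|---|---|---|
| n = 132, 20% events | 10 | 1.9 | 22% | 4.2% | 34% |
| | 15 | 3.0 | 23% | 4.6% | 49% |
| | 20 | 3.9 | 24% | 4.7% | 60% |
| n = 132, 42.9% events | 10 | 1.9 | 28% | 5.3% | 42% |
| | 15 | 3.1 | 23% | 4.8% | 50% |
| | 20 | 4.0 | 25% | 5.0% | 61% |
| n = 264, 20% events | 10 | 2.1 | 27% | 5.6% | 43% |
| | 15 | 3.0 | 25% | 5.0% | 52% |
| | 20 | 4.0 | 24% | 4.8% | 63% |

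The last column needs a comparator. Testing k independent null variables at .05 with no screen gives 1 − 0.95^k = 40%, 54% and 64% for k = 10, 15 and 20. The screened figures are of the same size, and they do not fall when events rise from about 26 to 53–57. They reflect the number of candidates tested and are not an effect of screening or of few events. What the screen distorts is the fourth column: the meaning of a p-value for a variable shown in the final model.

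**4. Clustering.** The 245 selected students in 12 classes make 245 / 12 = 20.4 per class, or about 10 of each sex. For a covariate constant within class, the variance is inflated by D = 1 + (m − 1) × ICC, and a nominal 5% test has type I error 2 × [1 − Φ(1.96 / √D)]. The documents give no ICC, and 0.05 is assumed.

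- m = 10: D = 1.45, 1.96 / √1.45 = 1.628, type I error 10.4%.
- m = 20: D = 1.95, 1.96 / √1.95 = 1.404, type I error 16.0%.

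Half that ICC (0.025) gives 7.7% and 10.7%. Twice that ICC (0.10) gives 15.5% and 25.0%.

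**The case against.** The strongest objection is that this is one secondary, largely descriptive analysis, and that a covariate list and a treatment of clustering may be in the full protocol or analysis plan, which are not shown. That stands as a limit on severity. It does not remove the point about selection, because the article states the entry rule itself and a fuller plan that followed it would have the same weakness. On clustering the objection carries more weight. The article names plain logistic regression and does not say that class will be ignored, so the concern applies to the model as described.

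A reader might also infer that the rule, applied with few events in each sex, will report chance predictors as barriers to vaccination. The documents do not support that:

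- The chance of at least one false positive comes from how many candidates are tested, and that number is not given. The rate per candidate is near nominal, and more events do not lower the overall chance. Few events cause instability, which is a separate problem.
- No initiation rate is stated, and there is no rate of any kind for boys.
- The sentence on separate analyses by sex precedes the model, and its reach over the model is only implied.
- The reported causes of nonvaccination are described separately, and interviews are also planned to determine barriers. The regression concerns predictors of initiation. Future Directions does not say that the regression will steer the program.

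**Conclusion.** The point holds as a weakness in method. Entry by bivariate p ≤ .20 does not meet the model's stated aim of dealing with confounding, and it makes the inference for retained variables optimistic. Under independent null covariates at n = 132 and 20% events, one that enters has a 22% to 24% chance of p < .05. Correlated or sparse covariates would change that figure. Estimates may also be unstable, with about 26 events among girls at the 20% completion rate, or 38 to 57 under the assumed 29% to 42.9%. As described, the model would give class-level covariates a type I error of roughly 10% to 16% at an assumed ICC of 0.05. The primary comparison is not affected. The change is worth making because it is cheap and uses data already collected.

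**What to change.** - Replace the p ≤ .20 rule with a short covariate list chosen on subject-matter grounds and fixed before the model is fitted. Include the sampling strata, grade and SEGPA status.
- Treat class as the cluster, with a small-sample correction for 12 classes.
- Use Firth penalisation if events are sparse.
- Report odds ratios with 95% confidence intervals as exploratory predictors of initiation, and keep the bivariate comparisons descriptive.
- State whether the model is fitted to girls and boys separately. Pooling them with a sex term would add events, and is an option rather than a requirement.

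The cost is a few sentences of analysis wording and no new data. Fewer variables would be explored in the multivariable model. Because the article reports that analyses were already ongoing, the date on which the list was fixed should be stated, so that readers can judge how far it was prespecified.
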